## 6 CLINICAL INVESTIGATION DESIGN

### 6.1 General

This clinical investigation is designed as a single center patient preference trial in a tertiary hospital in the Netherlands. We will test for non-inferiority of the outcome of the outpatient recovery after standard bariatric surgery compared to the current treatment, as well as evaluate the feasibility of the outpatient recovery after standard bariatric surgery.

To avoid bias, patient preference for either the current recovery path (group B) or the outpatient recovery (group A) after standard bariatric surgery is noted to be able to include the preference factor in the analysis. The patients that don't have a preference will be randomly assigned. The number of patients included in each group will be equal.

The primary endpoint of the study is the combined outcome measure, based on the following:

- Mortality
- Severe postoperative complications (Clavien-Dindo IIIb or higher)
- Readmission (at least one night in hospital)
- Mild complications (Clavien-Dindo II and IIIa)
- Prolonged length of stay (3 days or more in hospital)

within 30 days after primary surgery.

The secondary endpoints of the study are:

- Patient satisfaction >6 points (on a scale of 1-10)
- Percentage of patients recruited for the outpatient recovery after standard bariatric surgery group
- Percentage of patients with full adherence to protocol and randomization
- Percentage of missing data

|                                                                                                                    |              |                        |                  |                    |
|--------------------------------------------------------------------------------------------------------------------|--------------|------------------------|------------------|--------------------|
| Title: Clinical Investigation Plan                                                                                 |              | Author: [name] |                  | Philips restricted |
| DocID: ICBE-2-36455                                                                                                | Version: 3.0 | Date: 2020-DEC-08      | Status: Approved | Page: 22 of 44     |
| This document is based on Philips Research Template: Clinical Investigation Plan, ID: QR-TEM-57, Date: 2019-Mar-21 |              |                        |                  |                    |

- Percentage of false positive of the positive notifications from the Healthdot system
- Total number of false positive of the positive notifications from the Healthdot system
- Total number of false negative notifications from the Healthdot system
- The outcome of patients who choose HD versus patients who were randomized to HD on a combined outcome measure as defined for the primary endpoint.
- To evaluate the outcome of patients who choose HD versus patients who were randomized to HD on a combined outcome measure as defined for the primary endpoint.
- Number of adverse events in both groups
- Amount of pain medication taken on the day of surgery in both groups
- Percentage of clinical decisions made based on the Healthdot system, that changed when information from a telephone consultation was also included.
- Patient and health professional satisfaction (on a scale from 1-10) for both the outpatient recovery after standard bariatric surgery group as the current recovery path group
- The costs involved with outpatient recovery after standard bariatric surgery supported by Healthdot and the cost involved with the current recovery path, in the period up to 7 days after surgery.

For each patient, the parameters mortality, severe postoperative complications (Clavien-Dindo IIIb or higher), readmission (at least one night in hospital), mild complications (Clavien-Dindo II and IIIa) and prolonged length of stay (3 days or more in hospital) within 30 days after primary surgery will be determined from the patient medical record by the principal investigator. Patient satisfaction will be obtained through a questionnaire at the end of the 8-day study period. Healthcare professional satisfaction will be obtained through questionnaires after all patients have completed the study. Percentage of missing data will be determined at the end of the study. False positive and false negative notifications from the Healthdot system will be noted by the healthcare professional that receives the notifications. Clinical decisions made based on the Healthdot system, that changed when information from a telephone consultation was also included, will be noted by the healthcare professional that makes the decisions. The costs will be estimated for each patient, based on the events that occurred as noted in the patient medical file. The principal investigator will retrieve this information from the patient medical file. Costs calculation will include hospital stay, additional contacts, re-admission-hospital stay for mild complications (less than Clavien Dindo 3, like superficial woundinfection, dehydration, pain or worryiness patient).

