## Statistical design

This study is primarily designed to test for non-inferiority of outpatient recovery compared to regular treatment for bariatric surgery. The outcome measure that we will use for the analysis is a combined measure, based on the following:

- Mortality
- Severe postoperative complications (Clavien-Dindo IIIb or higher)
- Readmission (at least one night in hospital)
- Mild complications (Clavien-Dindo II and IIIa)
- Prolonged length of stay (3 days or more in hospital)

within 30 days after primary surgery.

We choose to use this combined outcome measure since it is in line with other surgical studies [5] making it comparable to literature.

I current practice at Catharina Hospital, Eindhoven, 95% of all bariatric surgery patients do not have any of these events which is considered the textbook outcome here.

We set the following null and alternative hypotheses for proving non-inferiority:

$H_0: p_{\text{regular}} - p_{\text{outpatient}} \geq \Delta$

$H_1: p_{\text{regular}} - p_{\text{outpatient}} < \Delta$

Where  $p_{\text{regular}}$  is the textbook outcome proportion in the regular treatment group, and  $p_{\text{outpatient}}$  is the textbook outcome proportion in the outpatient recovery group. We will use a non-inferiority margin ( $\Delta$ ) of 7%, which is deemed clinically significant by the Principal Investigator. This is also justified by a previous study where the average textbook outcome across bariatric surgery patients in the Netherlands was 88,7% [5] which helps to derive a non-inferiority margin of around 7% to the one seen at Catharina Hospital. We will use an uncorrected chi-squared statistic. Based on the sample size calculation done below an p value of 0.05 will be considered statistically significant. For the interim analysis an alpha correction for multiple testings is applied and a p value of 0.025 will be considered statistically significant.

The secondary endpoints will be analysed statistically in analogy to the primary endpoint by uncorrected chi-squared statistic where deemed appropriate.

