## Sample size

Sample size calculations were performed using PS: Power and Sample Size Calculation software. With a power of 0.80, an  $\alpha$  of 0.05, a non-inferiority margin of 0.07 and an expected proportion of 0.96, this resulted in a sample size of 97 (we choose 100) patients per group when using an uncorrected chi-squared statistic.

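### The principal investigator grades the primary-endpoint complications from a record that shows the recovery path, with no masking stated; a short masked extract would reduce this risk cheaply

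*Protocol*

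**What the plan says.** Section 6.1 (General) lists the five components of the primary endpoint: mortality, severe complications, readmission, mild complications and prolonged stay, all within 30 days. It then says that these "will be determined from the patient medical record by the principal investigator". The trial is "designed as a single center patient preference trial in a tertiary hospital in the Netherlands", with equal group sizes. The chart of an outpatient shows same-day discharge, the Healthdot and a day-2 teleconsultation; the chart of a regular patient shows an observed night on the ward (Section 6.4, Discharge from hospital and Table 1).

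The protocol text available states no masked grading, second reader or adjudication. One part of Section 14 was not available, so a review body described there cannot be excluded.

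The endpoint's mild class is the same wherever the endpoint is defined (Section 5, Section 6.1 and Section 7, Statistical design): "Mild complications (Clavien-Dindo II and IIIa". The last sentence of the endpoint paragraph in Section 6.1 uses the word mild differently, for costs: "re-admission-hospital stay for mild complications (less than Clavien Dindo 3, like superficial woundinfection, dehydration, pain or worryiness patient".

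**The concern.** A reader who knows the recovery path decides whether a complication reaches grade II, and that can decide whether the patient counts as a failure. At the site's stated 95% textbook-outcome rate, about 5 failures per 100 are expected in a group, so the non-inferiority result rests on few events. If borderline complications were graded more leniently in outpatients than in regular patients, the bias would run towards non-inferiority, which is the study's only success criterion (Section 7, Pass/fail criteria).

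**Working it through.** **Inputs.** Section 7, Sample size: "With a power of 0.80", alpha 0.05, "a non-inferiority margin of 0.07 and an expected proportion of 0.96", 97 per group rounded up to 100. Section 7, Statistical design: current textbook outcome 95%, so about 5 failures per 100. The sidedness of alpha is not stated.

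**The plan's own figure.** Non-inferiority for two proportions with equal true rates:

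n = (z₀.₉₅ + z₀.₈₀)² × 2p(1−p) / Δ² = (1.645 + 0.842)² × 2(0.96)(0.04) / 0.07² = 96.9, so 97.

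This matches the protocol. One-sided 0.025 would give 124, so the working uses one-sided 0.05.

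**Where one event decides.** Let x_R and x_O be the failures per 100 in the regular and outpatient groups. Non-inferiority is concluded if

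(x_O − x_R)/100 + 1.645 × √{[p_R(1−p_R) + p_O(1−p_O)]/100} < 0.07, with p = x/100.

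| Regular failures | Outpatient failures | Upper bound | Result |
|---|---|---|---|
| 4 | 5 | 5.82% | passes |
| 4 | 6 | 7.06% | fails |
| 5 | 6 | 6.30% | passes |
| 5 | 7 | 7.52% | fails |

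The pooled and Farrington-Manning score tests give the same limits in these rows. At one-sided 0.025 with 5 regular failures, 5 outpatient failures pass and 6 fail (7.32%).

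**How often the trial sits on that boundary** (exact binomial enumeration, unpooled test, one-sided 0.05). The trial misses by exactly one outpatient event in 9.4% of trials when both true failure rates are 4%, in 10.8% when both are 5%, and in 4.4% at 5% v 12%.

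**Effect on false non-inferiority.** True textbook outcome is 95% regular v 88% outpatient, a deficit equal to the margin. Lenient grading is represented by lowering the recorded failure rate.

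| Assumed leniency | Recorded failure rates, regular v outpatient | Probability of concluding non-inferiority |
|---|---|---|
| None | 5% v 12% | 5.9% |
| 1 per 100, outpatients only | 5% v 11% | 9.5% |
| 2 per 100, outpatients only | 5% v 10% | 14.9% |
| 1 per 100, both groups | 4% v 11% | 6.0% |

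The rise comes from a difference in leniency between the groups, not from leniency itself.

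**Which regrades count.** A change from IIIb to IIIa, or from IIIa to II, leaves the patient in the composite. A patient readmitted overnight or staying 3 days or more fails whatever the grade. Only a complication-only failure regraded below II leaves the composite. The protocol gives no count of these, so 1 and 2 per 100 are illustrations, not estimates.

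**The case against.** The case against has several parts.

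- **Two wordings of mild.** A reader might infer that the lower limit of the endpoint is not fixed. The documents do not support this. Grade II is the lower limit wherever the endpoint is defined, and the other wording describes a cost item. That item concerns a readmission stay, and a readmission of at least one night is already a failure at any grade. The wording needs only tidying.
- **Blinding considered and rejected.** A reader might infer that the protocol weighed masked assessment and turned it down. It does not discuss the subject.
- **Any downgrade flips the trial.** It does not: most regrades leave the composite unchanged, and the one-event flip exists only at the boundary. Any threshold test has such a boundary.
- **Direction of bias.** Nothing in the protocol shows that the investigator would treat the groups differently, and equal leniency leaves the error almost unchanged.
- **Existing safeguards.** Section 8 requires eCRF data to match the chart and keeps an audit trail; Section 6.5 refers to source data verification in a separate monitoring plan. These limit regrading against the record, but they do not mask the grader.

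These points limit the size of the concern. What stands is that the protocol fixes who grades and from what source, that the source reveals the group, and that no masking is stated.

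**Conclusion.** The point holds as a cheap improvement to how the endpoint is determined. It does not show that the result will be biased. One unmasked grading can decide the result only in the minority of trials at the boundary, and only through a complication-only failure near the I/II limit. If leniency were confined to outpatients at 1 or 2 failures per 100, false non-inferiority would rise from 5.9% to 9.5% or 14.9%; if shared equally, it would stay near 6.0%. These figures assume 100 per group, one-sided 5%, the unpooled test and true rates of 95% v 88%. The amount of differential leniency is an assumption that the documents can neither confirm nor exclude. That masking is absent is inferred from the text available.

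**What to change.** In Section 6.1, have the complications graded from a short coded extract giving the diagnosis, the treatment given and the day after surgery, with group, ward setting, Healthdot information and discharge day removed. The researcher described in Section 13.1 (Eligibility process) as not directly involved in surgery or care could prepare it, for every patient in either group with any recorded postoperative event. One written inclusion rule should apply to both groups, so that selection of events does not reintroduce the bias. The principal investigator can remain the grader.

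**Cost.** About 10 extracts in 200 patients at the site's 95% rate (5% × 200), and more once minor events are included. Masking stays incomplete for first-night events, where the paths differ most, and the preparer may know the group.

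The ungraded components (death, overnight readmission, stay of 3 days or more) may be reported descriptively. Passing a test on them at the same 7-point margin is weak reassurance: if they failed in 2% of each group (an assumption), that test would pass 95% of the time, against 73% for a composite failing in 5% of each group. The cost sentence could use a different term from mild for its below-grade-3 class; this changes no primary result.

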### Primary hypotheses

Outpatient recovery after standard bariatric surgery is not inferior to the current treatment based on a combined outcome measure.

The outcome measure that we will use for the analysis is a combined measure, based on the following:

- Mortality
- Severe postoperative complications (Clavien-Dindo IIIb or higher)
- Readmission (at least one night in hospital)
- Mild complications (Clavien-Dindo II and IIIa)
- Prolonged length of stay (3 days or more in hospital)

within 30 days after primary surgery.

This hypothesis will be accepted or rejected based on the outcome of the primary endpoint of this clinical investigation (for more details see page 33, Statistical considerations, Pass/fail criteria).

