- Patient and health professional satisfaction (on a scale from 1-10) for outpatient recovery after standard bariatric surgery with the Healthdot are equal or higher than for current treatment.
- The costs involved with outpatient recovery after standard bariatric surgery supported by Healthdot is less than the cost involved with the current recovery path, in the period up to 7 days after surgery.
- The usability of the visualization of Healthdot data on the Guardian dashboard is scored good (at least 4 out of 5).

These hypotheses will be accepted or rejected based on the outcome of this clinical investigation.

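### The cost rule counts readmission stay only below Clavien-Dindo 3, so a severe complication on the first night is costed in the regular group but not in the outpatient group

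*Protocol*

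**What the plan says.** The cost hypothesis (section 5, Secondary hypotheses) is that outpatient recovery with Healthdot support "is less than the cost involved with the current recovery path, in the period up to 7 days after surgery". The matching secondary endpoint in section 6.1 uses the same period.

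The method is in the last part of section 6.1. "The costs will be estimated for each patient, based on the events that occurred as noted in the patient medical file", and the calculation is then said to cover time in hospital, extra contacts and "re-admission-hospital stay for mild complications (less than Clavien Dindo 3". Examples of mild complications follow. Nothing elsewhere in the protocol brings in readmission stay for grade III or higher.

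Table 1 in section 6.4 gives the timing. The outpatient group is assessed for discharge around 20:00 on day 1. The regular group is observed overnight and discharged after an assessment around 12:00 on day 2.

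The primary endpoint counts severe complications and any overnight readmission "within 30 days after primary surgery". These events are therefore already extracted from the record, whatever the cost rule does with them.

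**The concern.** Section 3 says that the main purpose of the hospital night is to detect early complications such as bleeding. That is where the two paths differ most, and it is where the cost rule treats them differently. The same event counts as hospital stay if the patient is still in the ward, and as an uncosted readmission if the patient has gone home.

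The saved night is counted in full as a benefit of the outpatient path, while the most expensive consequence of leaving early falls outside the list. Section 3 names lower healthcare costs as a potential benefit, and section 5 says that claims may be derived from the secondary hypotheses. A favourable cost result obtained under this rule would be open to challenge.

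**Working it through.** The protocol states no cost figure, so there is none to reproduce. The check sets the cost rule against the discharge times and then asks how far the size can be bounded.

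**Which severe events are costed (grade III or higher, within 7 days)**

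| When the complication arises | Regular group | Outpatient group |
|---|---|---|
| Before about 20:00, day 1 | Index stay, costed | Index stay, costed |
| About 20:00 day 1 to about 12:00 day 2 | Index stay, costed | Readmission of grade III or higher, not costed |
| After about 12:00, day 2 | Readmission, not costed | Readmission, not costed |

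The middle row lasts 4 hours to midnight plus 12 hours, so 16 hours. The last row is treated alike in both groups unless early discharge itself raises the rate of severe readmission. An outpatient who is kept in because the discharge criteria are not met stays in the index admission and is costed normally.

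**Net omission**

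Let *w* be the proportion of patients with a severe complication in the 16-hour interval, *e* the excess proportion of severe readmissions caused by early discharge, and *L* the cost of one such readmission in ward-night equivalents. The outpatient cost per patient is understated, relative to regular care, by

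(*w* + *e*) × *L*.

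Neither *w* nor *e* can be negative if early discharge does not prevent severe complications, so the tilt is towards lower outpatient cost. If *w* = *e* = 0 there is no tilt.

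**Size, on assumed inputs only**

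The protocol gives none of *w*, *e* or *L*. Taking *w* + *e* from 1% to 5% and *L* from 5 to 40 night equivalents:

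| *w* + *e* | *L* = 5 | *L* = 10 | *L* = 20 | *L* = 40 |
|---|---|---|---|---|
| 1% | 0.05 | 0.10 | 0.20 | 0.40 |
| 2% | 0.10 | 0.20 | 0.40 | 0.80 |
| 5% | 0.25 | 0.50 | 1.00 | 2.00 |

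The comparison is with about one night saved per outpatient. The omission cancels that night when (*w* + *e*) = 1/*L*, which is 20%, 10%, 5% and 2.5% for the four values of *L*.

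Two facts argue for the low end. Section 7 says that 95% of the site's patients have none of the events in the composite. With equal complication rates (*e* = 0), *w* is therefore at most about 100% − 95% = 5%, and that 5% covers every event type over 30 days, not only severe events in 16 hours. Also, ward nights inside a 7-day window cannot reach 10 or more, so the larger values of *L* apply only if intensive care or reoperation is priced well above a ward night.

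**The case against.** The strongest reply is that the sentence in section 6.1 says what the calculation will cover, not that it covers nothing else. The sentence before it is wider, since it bases costs on the events in the medical file. This stands in part: a wider count is not expressly forbidden. But a rule that names readmission stay and then attaches a severity limit is naturally read as leaving out readmissions above the limit, and no other section corrects that reading.

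A second reply is that the limit applies to both groups. This also stands in part. After midday on day 2 a severe readmission is uncosted in either group, so the asymmetry is confined to the 16-hour interval and to any excess caused by early discharge.

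A reader might infer four stronger points, which the protocol does not support:

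- *That the 7-day window biases the result.* The window is the same in the hypothesis and the endpoint, applies to both groups and matches the 7 days of home monitoring. It would bias the comparison only if later costs differed between groups. A 30-day window is a preference.
- *That the Healthdot and its monitoring are left out of the cost.* They are not listed, but the list is not closed, the endpoint is defined as the cost of recovery with Healthdot support, and additional contacts could cover the teleconsultation. Detailed resource lists are commonly left to a later plan. The wording is unclear, but it does not exclude them.
- *That the two meanings of mild distort the result.* The primary endpoint has "Mild complications (Clavien-Dindo II and IIIa"), while the cost rule means below grade 3. The cost sentence defines its own term, so this is a labelling inconsistency.
- *That a set share of the saving goes uncounted.* Supposing 1 to 3 severe outpatient readmissions of 5 to 14 days gives 1 × 5 = 5 to 3 × 14 = 42 bed-days against 100 saved nights. That count is gross: it subtracts nothing for the regular group, its inputs are assumed, and a 14-day stay does not fit in the 7-day window.

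**Conclusion.** The concern holds for the severity ceiling. As written, the rule costs a severe complication of the first night in the regular group and not in a discharged outpatient, and it does not cost any excess of severe readmissions due to early discharge. Both push the comparison towards lower outpatient cost.

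The conclusion rests on reading the ceiling as an exclusion, on the approximate discharge times in Table 1, and on early discharge not reducing severe complications. Only the direction is supported. The size cannot be derived, and it may be small given how few of the site's patients have any event. The affected endpoint is secondary, and neither the primary non-inferiority test nor the pass/fail criterion depends on it. The correction is still worth making, because the flaw favours the hypothesis being tested and is easily removed.

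**What to change.** In section 6.1, remove the severity ceiling. State that, in both groups, all hospital stay, readmissions and reinterventions of any Clavien-Dindo grade within 7 days after surgery are costed. This also removes the second meaning of mild from the cost rule. State as well that the Healthdot, the scheduled day 2 teleconsultation and the daily dashboard review are part of the outpatient cost, as the wording of the endpoint implies.

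The 7-day window can stay. A 30-day cost figure may be added as an optional sensitivity analysis, since the record is read to 30 days for the primary endpoint anyway.

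The price is a change of wording and slightly more chart extraction. The cost result may become less favourable to outpatient recovery, and more variable, because a few expensive cases will carry weight.

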| Interview about dashboard with Healthcare professionals    |   |  |   |   |   |   |   | X |   |
| Healthcare professionals fill in questionnaire             |   |  |   |   |   |   |   |   | X |
| CRF completion, including 30-day readmission               |   |  |   |   |   |   | X |   |   |
| Adverse event documentation                                | X |  | X | X | X | X |   |   |   |
| Device accountability logging                              |   |  | X |   |   | X |   |   |   |

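### The cost rule counts the index stay at any severity but readmission stays only below Clavien-Dindo 3, which tilts the secondary cost comparison towards outpatient recovery

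*Protocol*

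**What the plan says.** The cost hypothesis in Protocol section 5, Secondary hypotheses, is directional: outpatient recovery with the Healthdot "is less than the cost involved with the current recovery path, in the period up to 7 days after surgery". The matching endpoint in section 6.1 General uses the same window.

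Section 6.1 then says how the costs are obtained. In general terms: "The costs will be estimated for each patient, based on the events that occurred as noted in the patient medical file". The components follow: the stay in hospital, extra contacts, and "re-admission-hospital stay for mild complications (less than Clavien Dindo 3". The examples given for the last item are minor ones such as superficial wound infection, dehydration and pain. Hospital stay carries no grade limit; the readmission stay does.

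The primary endpoint (section 6.1 General and section 7, Statistical design) counts complications from Clavien-Dindo II upwards and any readmission of at least one night, to day 30. The schedule in section 6.4 has a day-31 entry, "CRF completion, including 30-day readmission".

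**The concern.** A severe complication costs the hospital money whether it is treated before the first discharge or after a return to hospital. The listed components cost the first case and, on their natural reading, leave out the second. The two pathways differ in when the first discharge takes place, so the rule sorts the same clinical event into a costed or an uncosted category according to the group.

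Section 3 (Justification) says that the night in hospital serves chiefly to detect early complications such as bleeding. These are the events that the outpatient pathway moves from the index stay to after discharge. The rule therefore credits the saved night in full and can drop the cost of the severe events that this night would have contained.

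What is at stake is one secondary hypothesis. It is to be accepted or rejected, and under Claims and intended performance (section 5) product claims may be derived from it.

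**Working it through.** The protocol states no cost figure, so there is none to reproduce. The check sets the cost rule against the timetable and then shows how the bias scales.

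**Step 1: where the two groups diverge (section 6.4, Table 1).** Outpatients are assessed for discharge around 20:00 on day 1, the regular group around 12:00 on day 2. The gap is about 16 hours. Under the listed components, a severe event (grade III or higher) is treated as follows:

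| Event arises | Regular group | Outpatient group |
|---|---|---|
| Before about 20:00 on day 1 | index stay, costed | index stay, costed |
| Between the two discharge times | index stay, costed | readmission, not costed |
| After about 12:00 on day 2, to day 7 | readmission, not costed | readmission, not costed |

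Only the middle row is asymmetric, and it works in one direction.

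**Step 2: size at equal event rates.** Let r be the severe-event rate, the same in both groups; C the extra cost per event in bed-night equivalents; and D the share of these events that arise between the two discharge times. One night is saved per outpatient, so the true saving is 100 nights per 100 patients (device and call costs set aside). Then:

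apparent saving per 100 = 100 + 100 × r × C × D

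All three inputs are assumptions. For r there is one anchor: section 7 says that 95% of current patients have none of the composite events, so severe events should lie below 5%.

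- r = 2%, C = 20, D = 1: 100 + 100 × 0.02 × 20 = 140.
- Same r and C with D = 0.5: 120. With D = 0.25: 110.
- Low corner, r = 1%, C = 10, D = 1: 110.
- High corner, r = 3%, C = 30, D = 1: 190.
- Bed nights only: a 7-day window holds at most 7 nights, of which one is planned, so C is at most 6 (if the window cuts off the nights themselves). With r = 2% and D = 1 this gives 100 + 100 × 0.02 × 6 = 112.

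A value of C well above 6 therefore needs intensive-care days or re-interventions to be priced into the index episode. D = 1 is an upper bound.

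**Step 3: would the conclusion reverse?** Suppose instead that outpatients have an excess e of uncosted severe readmissions. The saved night is cancelled when C = (1 − o)/e, where o is the part of the night used up by device and calls.

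| e (percentage points) | 1 | 2 | 3 | 5 | 7 |
|---|---|---|---|---|---|
| Break-even C, o = 0 | 100 | 50 | 33 | 20 | 14 |
| Break-even C, o = 0.5 | 50 | 25 | 17 | 10 | 7 |

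At small excess rates, a reversal needs very expensive events. The protocol supplies neither e, C nor o.

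**The case against.** The strongest reply is that the component sentence says what the calculation will include, not that nothing else counts, and that the sentence before it bases costs on whatever events the medical file shows. This stands as far as wording goes: the exclusion of grade III and above is inferred, not stated. But a limit attached to readmission stays alone would serve no purpose if all grades were costed. If all grades are meant, the sentence still needs correcting.

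It is also fair to say that severe events are not hidden from the trial. They count in the primary endpoint to day 30, and adverse events are compared between groups. That limits the harm to the cost result.

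Three stronger readings are tempting, and the protocol does not support them.

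- **The 7-day window is itself an error.** The window, "in the period up to 7 days after surgery", is stated alike in the hypothesis and the endpoint, matches the week of home monitoring, and covers the early complications named in section 3. A cost horizon need not equal the clinical one. A 30-day figure is a useful addition, not a correction.
- **Omitted readmissions would overturn the cost conclusion.** Taking 2 to 7 extra readmissions per 100 at 3 to 10 nights each gives 2 × 3 = 6 to 7 × 10 = 70 nights, which stays below the 100 saved. The upper end also borrows the 7-point non-inferiority margin, which applies to the whole composite and not to readmissions.
- **Two definitions of mild create a contradiction.** The endpoint has "Mild complications (Clavien-Dindo II and IIIa", while the cost rule draws the line below 3. Each use carries its own grades, and the composite counts IIIa in any case, so the label changes no result. One term would read better.

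**Conclusion.** The point holds as an asymmetry in the cost rule. As naturally read, section 6.1 costs severe complications in the index stay and leaves them out when they lead to readmission. Events arising in the roughly 16 hours between the two planned discharge times are then charged to the regular group only. This overstates the saving from outpatient recovery even when event rates are equal.

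Under the assumed inputs above, with every event placed between the two discharge times, the overstatement is 10 to 90 bed-night equivalents per 100 patients, with 40 in the central case. It shrinks in proportion to the share of events that fall in that interval. On bed nights alone, at a 2% rate, it is at most 12. Acceptance of the hypothesis would change only if the true net saving were zero or negative and the bias large enough to hide it. Without unit costs this cannot be judged, so a reversal is not shown. The primary non-inferiority conclusion does not depend on any of this.

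**What to change.** In section 6.1 General, delete the grade limit on readmission stays. State that all hospital days, re-interventions and readmissions of any Clavien-Dindo grade are costed in both groups within the stated 7-day window, from the medical file that the principal investigator already reviews. Add the same calculation to day 30, matching the primary endpoint's follow-up, as a sensitivity analysis. No clinical procedure changes.

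The cost is a few more unit costs and some extra extraction. Section 6.4 (Follow up) mentions only whether a readmission occurred, so length of stay and procedures would have to be taken from the file for the few patients readmitted. The cost difference will also be more variable, because a handful of severe cases can dominate it. The analysis should report that uncertainty; it is no reason to leave those cases out.
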